#### Digital Interventions

##### Baseline (Usual Care) Web App

Online Study 1 will test the data gathering aspects of the proposed Web app using a baseline usual care intervention consisting of a static smoking cessation guide, *Guía Para Dejar de Fumar*, tested in printed form in the Muñoz et al study [13]. The print version of the guide yielded an 11% quit rate at 3 months. We will upload the content of the guide to the baseline app, and it will serve to estimate baseline utilization and quit rates.

##### The San Francisco Stop Smoking Web App

This Web app will be developed with input from the SFHN population. Thus, we are not able to provide a concrete description of the app at this time. However, our work to date has been guided by social learning/social cognitive theory and uses cognitive behavioral principles that will guide our thinking. Based on our experience with Web-based apps, we have found a number of features are valued by users. Users want information provided in a number of ways (text, graphics, audio, video, *telenovela*-type stories). Goal setting is important, so we will be looking for ideas for interactive goal-setting tools. Notifications are useful for bringing people back to the site or Web app, and we will ask our informants if they prefer them via text messaging or triggered by the app itself. We know that small behavior change steps can be encouraged using reinforcement, so we will be on the lookout for gaming ideas such as winning points and earning badges. We will ask for specific skills that our informants see as most useful (eg, saying no when offered cigarettes) and teach these skills using models. We will also consider social interaction tools (eg, smoking cessation buddies). However, the specific instantiation of these principles will stem from the participatory design process as defined by input from SFHN patients and health care providers. The exact structure of the intervention will be guided by participant input. Recent reports suggest using a hierarchical taxonomy to describe the active components of behavioral change intervention protocols [40]. We anticipate that active components of the intervention will include goal setting (behavior and outcome), self-monitoring, social support (practical and emotional), prompts/cues and cue signaling rewards, and behavioral practice/rehearsal.

#### Measures

##### Field Studies

User-centered design and usability testing aims to determine whether people can use the tools and features (ease of use) and how they like using them (usefulness). These questions will be addressed using a mix of qualitative (semistructured interview) and quantitative (satisfaction, acceptability, and perceived usefulness ratings) methods. Furthermore, during usability testing participants will be audio- and videotaped while interacting with the tools and features. Participants will report their overall satisfaction, as well as satisfaction with the design, content, functionality, and features. Participants will report what they liked best and least about the tools and features as well as strengths and weaknesses of the tools. Participants will rate the perceived usefulness of each aspect and the acceptability of using the program in the future.

##### Online Studies

To reduce participant burden, we will use reduced versions of the baseline and follow-up questionnaires we used in our earlier website-centered studies. Being asked to respond to long surveys on a mobile device is likely to result in high dropout rates. Therefore, we propose the following:

Eligibility: age, current smoker, speak English or Spanish.Baseline (obtained on the Web app when the smokers installs the app and gives consent to enter the study): demographics (age, sex, race, ethnicity, marital status, employment status, income, and educational level), smoking history (age first cigarette, age regular smoker, cigarettes per day, quit attempts, and methods used to quit), the Fagerström Test for Nicotine Dependence (6 items) [41], and rating of quit confidence.Follow-ups (brief and obtained using text messaging to increase completion rates): smoking status (7-day and 30-day point prevalence abstinence rates, operationalized as a “no” response to “Have you smoked 1 or more cigarettes in the last seven days?” and, if “no” to the previous question, “Have you smoked 1 or more cigarettes in the last 30 days?”); number of cigarettes per day smoked in the last week (if still smoking); and rating of confidence that the user will remain quit (if not smoking) or be able to quit in the next 30 days (if smoking).

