#### Hypotheses

H1: Utilization of the final smoking cessation Web app (number of screens viewed, time spent using app, and amount of data entry) will be significantly higher than that of the baseline Web app.

H2: Recruitment based on dissemination strategies derived from ethnographic interviews will reach a significantly higher number of participants for successive online studies.

H3: Abstinence rates (7-day self-reported abstinence) will be significantly greater for the final Web app than for the baseline Web app.

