#### Online Studies

##### Online Study 1: Baseline (Usual Care) Web App

A Web app will be developed to test the data-gathering infrastructure for the subsequent apps and generate baseline information on four variables: recruitment rates, utilization of the app, follow-up completion rates, and quit rates. Usual care is described in the Intervention section. We will engage in focused recruitment of smokers from the SFHN (up to 25 English speakers and 25 Spanish speakers) as well as open online recruitment with California as our main target (up to 50 English speakers and 50 Spanish speakers). We will implement follow-up interviews to examine quit rates at 1, 2, and 3 months after enrollment in the study. We will use 3 text messages (identified as coming from the Stop Smoking Study) 2 days apart. The first question will ask “Have you smoked 1 or more cigarettes in the last seven days?” A no response will be interpreted as 7-day point prevalence abstinence. Additional questions will address 30-day abstinence, number of cigarettes smoked daily if not abstinent, and use of other smoking cessation tools.

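### The abstinence items count only whole cigarettes, so a responder who still takes puffs or smokes part of a cigarette can truthfully be scored as quit

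*Protocol article*

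**What the plan says.** The abstinence question is given word for word in two places of the protocol article. The description of Online Study 1 states: "The first question will ask “Have you smoked 1 or more cigarettes in the last seven days". It then gives the scoring rule: "A no response will be interpreted as 7-day point prevalence abstinence". The Measures section for the online studies repeats the same definition, with abstinence "operationalized as a “no” response to “Have you smoked 1 or more cigarettes in the last seven days", and adds the 30-day item, which goes only to people who denied smoking in the 7-day window: "if “no” to the previous question, “Have you smoked 1 or more cigarettes in the last 30 days".

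The remaining follow-up items are limited. Online Study 1 lists them as follows: "Additional questions will address 30-day abstinence, number of cigarettes smoked daily if not abstinent, and use of other smoking cessation tools". In Measures, the consumption item is "number of cigarettes per day smoked in the last week (if still smoking"), so a person classed as abstinent does not receive it. Follow-up is brief and by text message, and no biochemical check is described.

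The item carries a main hypothesis: "H3: Abstinence rates (7-day self-reported abstinence) will be significantly greater for the final Web app than for the baseline Web app". The Data Analysis section for Online Study 4 plans on a quit rate of 10% with the baseline app and 20% with the final app (odds ratio 2.25), and treats people lost to follow-up as still smoking.

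**The concern.** The threshold is one or more cigarettes. A continuing smoker who took a few puffs, or who smoked less than a whole cigarette, can answer no without misreporting. The scoring rule then records that person as quit, and the plan calls the result a quit rate.

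The article fixes this explicitly: it gives both the question and the way the answer is scored. The outcome is self-reported by text and no probing is described, so the wording of the item decides who counts as abstinent.

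If continuing smokers are counted as quit at the same rate in both arms, both quit rates rise and the odds ratio moves toward 1. If the rate differed between arms, the contrast itself would be biased, in a direction that the document does not allow one to predict.

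**Working it through.** **Text check: does anything else catch such a person?**

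- The 30-day item has the same threshold, so it does not.
- The cigarettes-per-day item goes only to people still classed as smoking, so it does not.
- Treating missing as smoking affects only non-responders. It does not reclassify a responder who answers no, but it does limit how many people can be misread.
- No passage says that a puff or part of a cigarette counts as smoking.

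The gap in the definition is therefore confirmed.

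**Inputs for the size**

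- Quit rates *p*: 10% and 20%, missing counted as smoking (Data Analysis, Online Study 4).
- Sample: 800 + 200 = 1000, so 500 per arm with equal allocation. Equal allocation is assumed, in line with the equal per-version figures in the power analysis.
- Response rate *r*: not given for this trial. The team's TC3 studies (Prior Research and Interventions) had 57.3% at 6 months with phone follow-up and 23.2% when fully automated. These serve as an assumed range, beside complete follow-up (100%).
- Share *e* of responding continuing smokers who answer no: not in the documents. Assumed 3% to 5%.
- Two-sided alpha of 0.05, assumed.

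**The plan's own effect size.** (0.20/0.80) / (0.10/0.90) = 2.25, which reproduces. With no misreading, the two-proportion normal approximation gives 99% power at 500 per arm.

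**Formula.** Non-responders are already smokers by rule, so the group at risk is *r* − *p* and not 1 − *p*:

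observed rate = *p* + (*r* − *p*) × *e*

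**Equal error in both arms**

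| *r* | *e* | Baseline app | Final app | OR | Power at 500 per arm |
|---|---|---|---|---|---|
| 100% | 3% | 12.7% | 22.4% | 1.98 | 98% |
| 100% | 5% | 14.5% | 24.0% | 1.86 | 97% |
| 57.3% | 3% | 11.4% | 21.1% | 2.08 | 99% |
| 57.3% | 5% | 12.4% | 21.9% | 1.98 | 98% |

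Example for row 3: 0.10 + (0.573 − 0.10) × 0.03 = 0.1142, and 0.20 + (0.573 − 0.20) × 0.03 = 0.2112. The odds ratio is (0.2112/0.7888) / (0.1142/0.8858) = 2.08.

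**Unequal error with no true effect, as an illustration only.** Take 10% true quitting in both arms, 3% misread with the baseline app and 6% with the final app. The split has no source in the documents.

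| *r* | Baseline app | Final app | OR | Chance of a significant result for the final app |
|---|---|---|---|---|
| 100% | 12.7% | 15.4% | 1.25 | 23% |
| 57.3% | 11.4% | 12.8% | 1.14 | 10% |
| 23.2% | 10.4% | 10.8% | 1.04 | 4% |

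The nominal chance in that direction is 2.5%. The 23% figure needs complete follow-up, which the team's earlier online studies did not come near.

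**The case against.** The strongest case on the other side is that this is a refinement of wording with an unknown and probably small effect. Several parts of it stand.

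- **Non-response limits the harm.** Only people who reply can be misread. Applying the error to every non-quitter overstates the effect. The calculation above allows for this.
- **Power is hardly touched.** With equal error, 500 per arm keeps at least 97% power in every case shown.
- **The planning rates may already contain the error.** The 10% and 20% come from the team's earlier studies, and Measures says the questionnaires are reduced versions of the earlier ones. If the item was carried over, adding misreading on top counts it twice. The item used in those studies is not shown, so this cannot be settled.
- **Some people who only puffed will answer yes.** The documents do not say how many.

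A reader might draw two stronger conclusions, and the documents support neither.

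The first is that the item favours the final app, because that app would encourage cutting down while the control is a static guide. The supporting sentence is "We know that small behavior change steps can be encouraged using reinforcement", and it goes on to points and badges, not to smoking part of a cigarette. The same section says that the app cannot yet be described concretely. Nothing there predicts more puff-only smoking in one arm.

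The second is that the item is wrong because it ignores cigars and other tobacco. The plan frames its outcome and most of its baseline smoking items around cigarettes and never promises tobacco abstinence. Extending the item to all tobacco would change the endpoint rather than repair it.

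What the objection does not remove is the definition itself: as written, it scores some continuing cigarette smokers as quit, and nothing downstream corrects that.

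**Conclusion.** The point holds as a gap in the definition of the 7-day and 30-day abstinence items. A responder who took only puffs or smoked part of a cigarette can truthfully answer no and be counted as quit.

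The size cannot be derived from the documents. If 3% to 5% of responding continuing smokers are misread equally in both arms, and 10% and 20% are the true rates, the odds ratio falls from 2.25 to about 2.08 to 1.98 at 57.3% response, and to 1.98 to 1.86 with complete follow-up. Loss of power at 500 per arm is small. The main consequence is that reported quit rates are somewhat too high and the odds ratio somewhat too close to 1.

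A false finding for the final app would need unequal misreading between arms, which is possible but not shown. This is a cheap improvement to a key outcome, not a flaw that invalidates the trial.

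**What to change.** Before Online Study 4 starts, reword both follow-up items in English and Spanish, identically in both arms, to: *Have you smoked a cigarette, even a puff, in the last 7 [30] days?* A no answer continues to mean abstinent. Change the definition in the Measures section to match.

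The work is the rewording of two text messages. It adds no question, so it respects the plan's aim of keeping follow-up short. The price is slightly lower quit rates and less exact comparability with Online Studies 1 to 3 and with the earlier rates used for planning. Enrollment is already under way, so the report should state which wording each online study used. The randomized comparison is not harmed as long as both arms receive the same text throughout.

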#### Data analysis

##### Ethnographic and Field Testing Phases

Mixed-methods data analysis will incorporate qualitative data from patient and therapist feedback; quantitative data from the satisfaction, acceptability, and usefulness ratings; and audio recordings from the field tests. Although quantitative ratings can highlight possible usability concerns, qualitative data provide answers to why those features might cause problems in ways that can guide development. Qualitative data will be interpreted following a grounded theory approach in which results from the semistructured interview will be analyzed using a series of codes to determine patterns in topics related to patients' and therapists' needs, concerns, and impressions of the prototype. Grounded theory was selected because it is a useful methodology for determining common topics within qualitative data to inform future practices and research. For the usability phase, we believe the users will raise unanticipated concerns and needs and thus we selected an approach that is flexible. Mean values of ratings from individual tools and features will be computed to identify those that require further refinement. Any tool or feature that is given the lowest value on a quantitative rating scale will be flagged for more intensive review in the video recordings and screen captures. Audio recordings and screen captures will address ease of use and be coded to determine three types of errors: navigation errors refer to instances when users cannot locate a function or have difficulty with aspects of the screen flow, content errors refer to instances of problems due to labeling or information presented, and usage errors refer to improper tool use or data field entry. Qualitative and quantitative data will be integrated through linking categories identified using the grounded theory approach with ratings on tools and features. Tools and features must score a mean value in the satisfactory range to be included in the next version. We will consider developing additional tools and features for other categories identified by users. Consistent with principles of constant comparative analysis, the principal investigator will make final decisions regarding tools and features.

##### Online Studies 1, 2, and 3

These studies are intended to provide continuous quality improvement data as a baseline smoking cessation intervention (a static stop smoking guide) moves through two iteratively designed versions of a user-centered Web app. The final version of the Web app will be evaluated in comparison to the baseline app. We will examine successive changes in recruitment rates, utilization of the app, follow-up rates, and quit rates. We will use observed changes or lack thereof to pinpoint areas that need improvement; this will help prioritize changes in recruitment media and messages, Web app functionality, text messaging issues, and elements of the Web app likely to increase quit rates.

##### Online Study 4

Participants will be randomly assigned to use either the baseline app or the final version of the San Francisco Stop Smoking Web app. We will focus our analysis on quit rates and use of the app. Latency (time spent) on content pages will be compared across the two versions of the app using independent samples *t* tests. Based on a Cohen designation of a small effect size for group mean comparisons of 0.2, a priori power analyses revealed a necessary sample size of N=800 (400 per version) to achieve a power of .80. Quit rates (smoking cessation status at 7- and 30-days) will be evaluated at 1, 3, and 6 months following registration, with individuals lost to follow-up treated as still smoking. To examine quit rate as a function of website version and demographic characteristics, logistic regression analyses will be conducted with quit status as the criterion variable; website version as the focal predictor; and gender, age, ethnicity, race, and income entered as covariates. Prior research suggests a usual care quit rate of 10% based on the 11% quit rate finding for the printed version of the *Guía Para Dejar de Fumar* in the Muñoz et al [13] study and missing=smoking rates ranging from 6.0% to 14.5% in our online studies [16,18,20]. We have estimated the quit rate of the improved, user-centered Web app at 20% based on the 23% quit rate found for the combined intervention in a later Muñoz et al study [13] and the best estimates of our online website, which yielded a missing=smoking rate of 20.2% for Spanish speakers and 21% for English speakers [16]. We estimate an increase of 10% (ie, improved website will result in 20% quit rate compared to a 10% quit rate for the baseline app), which results in an odds ratio of 2.25. This odds ratio was used as the effect size estimate in an a priori power analysis that yielded a total sample size of N=550 (225 per site version) to achieve power of .80.

We estimate needing a minimum of 800 participants to detect small effect sizes in utilization and 550 to detect clinically significant differences in quit rates. We therefore propose to recruit 800 participants via the open online recruitment process (to reach the minimum sample size estimated in our power analysis) and an additional 200 SFHN participants to increase our sample size and carry out secondary subgroup analyses to determine whether utilization and quit rates for the SFHN patients appear similar to those recruited outside the SFHN.

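### The quit-rate sample size does not add up: two versions at 225 make 450, not 550, and 550 for power .80 cannot be reproduced from the stated inputs

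*Protocol article*

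**What the plan says.** The Online Study 4 part of the data analysis section gives two power calculations for the randomized comparison of the final app with the baseline app.

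- **Utilization:** a standardized mean difference of 0.2 and power .80 lead to 800 participants, 400 per version.
- **Quit rates:** the assumption is that the "improved website will result in 20% quit rate compared to a 10% quit rate for the baseline app". The article converts this difference to an odds ratio of 2.25 and takes that as its effect size. The calculation then "yielded a total sample size of N=550 (225 per site version) to achieve power of .80".

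The following paragraph sums up the two requirements as "800 participants to detect small effect sizes in utilization and 550 to detect clinically significant differences in quit rates". From there it sets recruitment at 800 through open online channels, with 200 San Francisco Health Network (SFHN) patients added.

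Neither calculation states alpha or sidedness. No inflation for dropout, covariates or multiple time points is mentioned. Participants lost to follow-up count as smokers.

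**The concern.** The total and the per-version figure stand in one sentence and cannot both be right for a two-version trial. This is the only sample-size statement for the abstinence hypothesis (H3), and the description of Online Study 4 refers the reader to this section for the trial's power on quit rates. If neither figure can be recovered from the stated rates and power, a reader cannot check what the quit-rate calculation assumed. The larger question is whether the slip leaves the trial short of participants for H3.

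**Working it through.** **Inputs from the article (Online Study 4 data analysis).** Control quit rate p1 = 0.10; intervention quit rate p2 = 0.20; odds ratio 2.25; power .80; two versions; a single per-version figure, which implies 1:1 allocation.

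**Assumed.** Two-sided alpha 0.05 and no inflation. Neither is stated.

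**1. The plan's own arithmetic**

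- Odds ratio: (0.20/0.80) / (0.10/0.90) = 2.25. This reproduces.
- Utilization: 2 x 400 = 800. Consistent.
- Quit rates: 2 x 225 = 450, not 550. The gap is 100 participants; 550/2 = 275.

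**2. Is two-sided 0.05 a fair assumption?** Apply it to the utilization calculation:

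n per version = 2(1.960 + 0.842)² / 0.2² ≈ 392.4, so 393 per version and 786 in total. That is within 3% of the stated 800, so the assumption fits the companion calculation.

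**3. Size needed for 10% versus 20% at power .80**

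*Pooled two-proportion formula.* With mean rate 0.15:

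n = [1.960 x √(2 x 0.15 x 0.85) + 0.842 x √(0.10 x 0.90 + 0.20 x 0.80)]² / 0.10² = [1.960 x 0.5050 + 0.842 x 0.5]² / 0.01 = 198.96, so 199 per version, 398 in total.

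*With continuity correction.*

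n' = (198.96/4) x [1 + √(1 + 4/(198.96 x 0.10))]² = 218.5, so 219 per version, 438 in total.

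*Wald formula on the log odds ratio*, the closest to the planned logistic regression:

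n = (1.960 + 0.842)² x (1/0.10 + 1/0.90 + 1/0.20 + 1/0.80) / (ln 2.25)² = 7.849 x 17.361 / 0.6576 = 207.2, so 208 per version, 416 in total.

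Unpooled and arcsine versions give 394 and 390. The range is therefore about 390 to 440, and none of these results is near 550.

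**4. Power at the printed figures** (pooled formula, two-sided 0.05)

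Power = Φ{[0.10√n − 1.960 x 0.5050] / 0.5}

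| Per version | Total | Power, 10% vs 20% |
|---|---|---|
| 225 | 450 | Φ(1.021) = 84.6% |
| 275 | 550 | Φ(1.337) = 90.9% |
| 400 | 800 | 97.8% |
| 500 | 1000 | 99.4% |

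Fisher's exact test gives slightly lower values: 82% at 225 and 89% at 275 per version. With 500 per version, the same power formula applied to 10% versus 16% gives about 80%.

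**5. What would produce 550 at power .80?** Each of these routes needs an input that the article does not give:

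- Dropout of about 28%: 398 / 0.72 ≈ 553.
- A covariate R² of about 0.25 in the log-odds-ratio formula: 2 x 207.2 / 0.75 ≈ 553.
- Alpha 0.05/3 for three follow-up times, log-odds-ratio formula: about 553.
- One-sided alpha 0.01 with continuity correction: 550.

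**The case against.** The best case on the other side is that only the mismatch between 450 and 550 is certain. Alpha is not printed, and an article may leave such inputs to the full protocol or analysis plan, which is not shown. Quit rates are assessed at 1, 3 and 6 months, so an alpha of 0.05/3 is conceivable and gives about 553. The alpha that fits the utilization calculation need not be the one used for quit rates. This stands. A reader might infer that 550 is proven wrong for power .80; the documents support only that it cannot be reproduced from the stated inputs.

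The other routes to 550 are less plausible. Dropout inflation sits badly with counting the lost as smokers, because every randomized participant stays in the denominator. Demographic covariates should be nearly uncorrelated with a randomized version, so an R² near 0.25 is not expected. One-sided 0.01 would require about 1004 for utilization, against the stated 800. None of these routes makes 225 per version consistent with 550.

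It is also fair to say that the practical effect is small. The planned size is clear, at 800 plus 200, and the larger requirement is utilization. The text says openly that quit rates need fewer participants, so a charge that it hides the surplus would be unfair.

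A reader might further infer which figure is the misprint. The evidence points both ways: 550 appears twice and 225 once, while 225 lies close to the continuity-corrected 219. Only the authors can settle it.

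**Conclusion.** The point holds as a minor reporting error. The sentence contradicts itself by 100 participants, with no assumption needed, and the unsupported total is carried into the recruitment rationale. At an assumed two-sided 5% alpha and no inflation, the stated effect needs about 400 to 440 in total for power .80. The printed figures correspond to about 85% power (225 per version) or 91% (275 per version).

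A reader might take this to mean that the trial is too small for H3. The documents do not support that: both printed figures exceed .80 under the stated rates, and the planned 800 to 1000 give about 98% to 99%. No recruitment target or analysis depends on which figure is correct.

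**What to change.** - Correct the quit-rate sentence so that the total is twice the per-version figure, and carry the same total into the next paragraph.
- State the alpha, sidedness, formula or software, and any inflation or multiplicity adjustment used.
- Restate the power that belongs to the corrected size. At two-sided .05 this is about .85 for 225 per version (450) or about .91 for 275 per version (550). If an unstated adjustment led to 550 at .80, say what it was.
- Optionally, add that the planned 1000 (500 per version) gives about 99% power for 10% versus 20% and about 80% for 10% versus 16%.

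The cost is a few lines of text. Recruitment, design and analysis are unchanged.
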